##### Carer-related quality of life

The CarerQol instrument (7 items) [45] and the Parenting Stress Questionnaire (34 items) [46] are aimed at measuring carer-related quality of life in informal caregivers. The CarerQol is an easy to use instrument and the Dutch version demonstrates good feasibility and construct validity [45]. Items are scored on a 3-point scale ranging from 0 (*none*) to 2 (*a lot*) with higher scores reflecting more burden experienced by the parent. The Dutch Parenting Stress Questionnaire (PSQ: English translation of ‘Opvoedingsbelasting Vragenlijst (OBVL)’) shows good internal consistency (Cronbach’s α from .89 to .91) and demonstrates construct validity [46]. Items are scored on a 4-point scale ranging from 1 (*not applicable*) to 4 (*completely applicable*) with higher scores indicating more parenting stress problems.

##### Parenting styles and family functioning

Family functioning and parenting styles are assessed using two validated Dutch questionnaires: the Family Functioning Questionnaire (FFQ: English translation of ‘Vragenlijst Gezinsfunctioneren Ouders (VGFO)’) [47] and the Brief Scale of Parental Behavior (BSBP: English translation of ‘Verkorte Schaal voor Ouderlijk Gedrag (VSOG)’) [48]. These are used to assess changes in family functioning and pedagogical style during treatment. The 28 items of the FFQ can be answered on a 4-point scale ranging from 1 (*not applicable*) to 4 (*completely applicable*) with lower scores indicating more problems in family functioning. The 25 items of the BSBP can be answered on a 5-point scale ranging from 1 (*(almost) never*) to 5 (*(almost) always*). Lower scores on two subscales indicate inadequate parenting styles, whereas higher scores on the three remaining subscales indicate inadequate parenting styles.

##### Satisfaction

Satisfaction and compliance is measured using the GGZ-Thermometer (http://www.ggznederland.nl/leden/thermometer/handleiding.html). This instrument allows Dutch institutions to examine how children and parents appreciate the care provided. Parents assess their satisfaction about the information they received about the treatment, amount of shared decision making, the team of psychologists and the result of the treatment. Also, parents assess experiences of the child about the treatment trajectory and of parents’ own treatment (if applicable). Finally, parents can rate their overall treatment trajectory on a scale of 0 to 10.

##### Cost measurements

Healthcare resources use, patient and family costs and productivity losses (absence from work of parents) as a consequence of the child’s psychiatric disorder are measured using the Dutch ‘Trimbos and iMTA questionnaire on Costs associated with Psychiatric illness’ (Tic-P questionnaire) [49]. Validity and reliability have been established [49]. The number of all health care contacts is registered with a 3 month recall period. These data are used to calculate the cost-effectiveness of the dietary conditions compared to CAU at 12 months of follow-up.

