### Procedures

Families who are interested to participate in the TRACE study are informed via telephone and information letters (sent via e-mail). Families can choose whether they want to participate in the dietary treatment arms or the CAU arm. If they choose a dietary treatment, they will be randomly assigned to either the elimination diet or the healthy diet.

If the eligibility criteria are met, parents are invited for an intake with a researcher to explain further details of participation, plan appointments and to disclose which diet the child is randomized to via a sealed envelope. Both parents fill out a written informed consent for the TRACE study (Additional file 1). If children are 12 years old, they also need to sign the consent forms. In addition, teachers are informed about the study via e-mail and general practitioners via postal letters.

Assessments will take place at baseline (T0), after five weeks of treatment (T1), after four (T2), eight (T3) and 12 (T4) months after start of treatment (i.e. dietary treatment or CAU). T0 will be scheduled within two weeks prior to the start of the treatment. Medication treatment prior to the dietary treatment has to be discontinued no later than one week before start of the diet. T0, T1 and T4 assessments will take place at one of the two participating sites. For the T2 and T3 assessments, parents are asked to fill out questionnaires online. Teachers are asked to fill out online questionnaires at T0, T1 and T4. Figure 1 depicts a flowchart on recruitment and procedure of the study.

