**Secondary outcomes**		
Blinded ADHD assessment	T0, T1, T4	DB-DOS
Parent & teacher comorbidity ratings	T0, T1, T4	SDQ, CSBQ, BRIEF, UPPS-P, EDI
Cognitive performance	T0, T1, T4	COTAPP
School performance	T0, T4	Monitoring system Dutch education
Motor activity and sleep pattern	T0, T1, T4	Actigraph
Physical measurements	T0, T1, T4	Weight, height, blood pressure, heart rate
Somatic complaints	T0, T1, T2, T3, T4	Pittsburgh side-effects rating scale
Sleep problems	T0, T1, T2, T3, T4	5-item questionnaire
Quality of life	T0, T1, T2, T3, T4	EQ-5D
Food consumption & eating habits	T0	Questionnaire dietary pattern
	T0, T4	Nutritional assessment (‘Eetmeter’)
Nutritional quality	T0, T2, T3, T4	Nutritional assessment (‘Eetmeter’)^b^
	T0, T1, T2, T3, T4	Expert view
	T0, T1, T4	Blood sample
Carer-related quality of life	T0, T1, T2, T3, T4	CarerQol, PSQ
Parenting styles and family functioning	T0, T1, T4	FFQ, BSBP
Adherence	T1, T4	Morisky Adherence Scale, food diary, separate questions
Satisfaction	T1, T4	GGZ-Thermometer
Cost measurements	T1, T2, T3, T4	Tic-P

*WPPSS-III* Wechsler Preschool and Primary Scale of Intelligence, *WISC-III* Wechsler Intelligence Scale for Children, *GHQ* General Health Questionnaire, *SWAN* Strengths and Weaknesses of ADHD-symptoms and Normal-behaviors (SWAN) rating scale, *SDQ* Strength and Difficulties Questionnaire, *DB-DOS* Disruptive Behavior Diagnostic Observation Schedule, *CSBQ* Children’s Social Behavior Questionnaire, *BRIEF* Behavior Rating Inventory of Executive Function, *UPPS-P* Urgency, Premeditation, Perseverance, Sensation seeking, and Positive urgency Impulsivity scale, *EDI* Emotion Dysregulation Inventory, *COTAPP* Cognitive Task Application, *PSQ* Parenting Stress Questionnaire, *EQ-5D* EuroQol Five Dimensions Health Questionnaire, *FFQ* Family Functioning Questionnaire, *BSBP* Brief Scale of Parental Behavior, *Tic-P* Trimbos and iMTA questionnaire on Costs associated with Psychiatric illness’

^a^T0 baseline; T1 five weeks after baseline; T2 four months after baseline; T3 eight months after baseline; T4 12 months after baseline. ^b^ Only parents of healthy diet participants who continue the diet after five weeks, register food consumption at T2 and T3

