For the cost-effectiveness analysis, all cost data will be accumulated over the 12 months period. Cost differences between the two dietary conditions and CAU will be compared. Incremental cost-effectiveness ratios will be calculated by dividing cost differences between treatments by differences in Quality Adjusted Life Years, as estimated from EQ-5D scores. Uncertainty analysis using 5000 bootstraps will be performed and cost-effectiveness planes and cost-effectiveness acceptability curves will be plotted.

The impact of missing data on the outcome measurements will be evaluated using different methods, such as Last Observation Carry Forward (LOCF) and Multiple Imputation (MI).

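### The 3-month cost recalls at 5 weeks, 4, 8 and 12 months cover only 10 of the 12 months over which costs are to be accumulated, and reach back before baseline

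*Protocol article*

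**What the plan says.** Under Cost measurements, the protocol article states: "The number of all health care contacts is registered with a 3 month recall period". It then gives the purpose: "These data are used to calculate the cost-effectiveness of the dietary conditions compared to CAU at 12 months of follow-up".

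The timing is in Table 3. Its row reads "Cost measurements T1, T2, T3, T4 Tic-P", so no cost form is taken at T0. Footnote a defines the visits: "T1 five weeks after baseline; T2 four months after baseline; T3 eight months after baseline; T4 12 months after baseline". The Procedures section instead counts the visits from the start of treatment and adds: "T0 will be scheduled within two weeks prior to the start of the treatment".

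Under Statistical analyses, "all cost data will be accumulated over the 12 months period". Cost differences are then divided by differences in QALYs estimated from the EQ-5D, which Table 3 schedules at every visit from T0 to T4. Uncertainty is described with 5000 bootstraps, cost-effectiveness planes and acceptability curves.

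**The concern.** The visits after T1 are about three to four months apart, while each form looks back three months. T3 and T4 each follow four months after the previous visit, so each leaves a month unasked. T1 comes only five weeks after baseline, so most of its window lies before the study began. With no form at T0, the pre-baseline contacts in the T1 answer cannot be identified and removed.

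The incremental cost-effectiveness ratio is at stake. Its denominator can be built from EQ-5D scores spanning the whole follow-up. The contact costs in its numerator would describe 10 of those months plus some earlier time. Bootstrapping resamples the same misaligned totals, so it would not reveal the problem.

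**Working it through.** **Inputs**
- Recall length: 3 months, stated for health care contacts (Cost measurements).
- Cost forms: T1, T2, T3, T4 (Table 3).
- Visit times: 5 weeks, 4, 8 and 12 months after baseline (Table 3, footnote a). Five weeks = 35 / 30.44 = 1.15 months.
- Horizon: 12 months, costs accumulated (Statistical analyses).
- T0 lies 0 to 2 weeks before treatment start (Procedures). Two weeks = 14 / 30.44 = 0.46 month.

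**Step 1: the windows.** Each form at time t covers t − 3 to t.

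| Form | Window (months) | Part within 0–12 |
|---|---|---|
| T1 | −1.85 to 1.15 | 0 to 1.15 |
| T2 | 1 to 4 | 1 to 4 |
| T3 | 5 to 8 | 5 to 8 |
| T4 | 9 to 12 | 9 to 12 |

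**Step 2: can the 12 months be reproduced?** Only as a plain sum: 4 × 3 = 12. The sum breaks down as follows.
- Covered within the horizon: T1 and T2 together 0 to 4, then 5 to 8 and 9 to 12, so 4 + 3 + 3 = 10 months.
- Before baseline: 3 − 1.15 = 1.85 months, about 8 of the 13 weeks in the T1 window.
- Counted twice (T1 and T2): 1.15 − 1 = 0.15 month.
- Check: 10 + 1.85 + 0.15 = 12.

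Never asked about: months 4–5 and 8–9, so 12 − 10 = 2 months, or 2 / 12 = 17% of the horizon.

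**Step 3: other readings of the timing**

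| Reading | Months not covered | Months before T0 |
|---|---|---|
| Visits counted from baseline (Table 3) | 2.0 | 1.85 |
| Recall taken as 13 weeks | 2.02 | 1.84 |
| Five weeks taken as 1.25 months | 2.0 | 1.75 |
| Visits counted from treatment start, T0 two weeks earlier | 2.0 | 1.85 − 0.46 = 1.39 |

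The two-month gap holds under every reading. The time before T0 ranges from 1.39 to 1.85 months. In the last row, 1.85 months still precede the start of treatment.

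**Step 4: does dropping T1 alone help?** No. With an unchanged 3-month recall, T2 to T4 cover 3 × 3 = 9 months and leave months 0–1, 4–5 and 8–9 unasked.

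**The case against.** The strongest reply is that accumulating costs over 12 months need not mean adding four raw totals. Resource use can be sampled in windows and scaled or interpolated, and such a rule usually sits in a full protocol or analysis plan that is not shown here. This stands in part: the harm arises only if the forms are summed without adjustment, and leaving out an interpolation rule would be no fault in an article. But the article itself fixes the schedule, the recall and the horizon, and these three do not fit. Analysis can only apportion the T1 answer by assumption, because no T0 form exists to separate earlier contacts.

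A reader might infer that the cost of medication stopped before the diet is charged to the diet groups. The article does not support that. It states the 3-month recall for health care contacts and gives none for medication, family costs or productivity losses.

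A reader might also infer that the comparison with care as usual is biased by a known amount. That is not supported either. Table 3 gives one schedule for all groups, and the Measurements CAU section does not list the Tic-P among the forms that CAU families skip. Every group therefore has the same gaps and the same look-back. Randomization should balance pre-baseline use between the two diets in expectation. Cancellation against CAU cannot be assumed: that group is not randomized, diet families must stop medication before starting, and they may move to CAU after five weeks. This makes a bias plausible but does not measure it. The 17% is a share of calendar time, not of cost.

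Finally, cost-effectiveness is a secondary aim. The primary outcome and its analysis are untouched.

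**Conclusion.** The point holds for health care contacts. As scheduled, the recalls observe 10 of 12 months, include about 1.4 to 1.85 months before baseline and count about 0.15 month twice. Summed as they stand, they appear to total 12 months, but the resulting contact costs do not describe the follow-up over which the QALYs are measured.

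This rests on two assumptions: that the 3-month recall applies to every form, T1 included, and that no adjustment is made before costs are accumulated. The article states no exception to the first and describes no adjustment. The size and direction of the effect on the cost-effectiveness ratio cannot be derived from it. The matter should be corrected for the economic evaluation and has no bearing on the primary comparison.

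**What to change.** **Forms still to be completed.** Ask at T1 about the time *since the start of treatment*, and at T2, T3 and T4 about the time *since the previous questionnaire*. The windows then join without gap or overlap.

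**Forms already completed.** State the following scaling in the analysis plan:
- T1: keep the post-baseline share, 5 of 13 weeks (3 × 5/13 = 1.15 months).
- T2: scale to the time since T1, factor 2.85/3 (2.85 months).
- T3 and T4: scale by 4/3 (4 months each).
- Total: 1.15 + 2.85 + 4 + 4 = 12 months.

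The T2 factor is needed. With T2 left at its full 3 months the total would be 1.15 + 3 + 4 + 4 = 12.15, and the overlap would still be counted twice.

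**Sensitivity analysis.** Drop T1 and scale T2, T3 and T4 each by 4/3, giving 4 + 4 + 4 = 12 months. This avoids apportioning the T1 answer but assumes that use in month 0–1 resembles use in months 1–4. That is open to doubt, because other treatment is restricted in the diet groups during the first five weeks.

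Also state the recall period for medication, family costs and productivity losses, and whether the 12 months run from T0 or from treatment start.

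**Cost.** A change of question wording and a few lines of analysis code. The downsides are a slightly longer recall at T3 and T4, two recall wordings within one trial (to be flagged in the analysis), and an assumption of even use within each scaled window.

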#### Descriptives

##### Prior beliefs

Parents prior beliefs about the short-term and long-term success and burden of dietary intervention and CAU are evaluated using a 5-item questionnaire in which parents rate their prior beliefs on a 5-point scale ranging from 0 (*completely disagree*) to 5 (*completely agree*). This measurement also will be used to examine successful randomization, by verifying whether the three groups differ in beliefs about the effectiveness of the intervention at baseline.

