### Study design

#### Randomization

Originally, the TRACE study was a three arm randomized controlled trial: participants were randomized to an elimination diet, healthy diet or CAU. However, randomization across a dietary intervention versus CAU proved not feasible. Parents usually had a strong preference towards either a dietary intervention or CAU. This resulted in an extremely slow inclusion rate, a high number of drop-outs and thereby unrepresentative groups of CAU. Therefore, after inclusion of 17 participants, the design was changed into a two arm randomized controlled trial (elimination diet vs. healthy diet) with a non-randomized comparator arm (CAU). Participants interested in a dietary intervention are randomized (50:50) to either an ED or a healthy diet with randomization within each participating center. Randomization by means of minimization is performed, including sex and age as factors, resulting in four groups. Within each group, blocked randomization is used (block size eight). The non-randomized comparator arm includes children who are being treated with CAU. Researchers disclose the group allocation to parents via a sealed envelope. Participants, researchers and dieticians are aware of treatment allocation. Researchers who will code the behavior observation (see secondary outcomes) are blinded to group allocation and time of assignment.

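### The check of successful randomisation compares prior beliefs across three groups, although only the two diet groups are randomised and families choose CAU

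*Protocol article*

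**What the plan says.** The Prior beliefs paragraph of the protocol article describes a 5-item parent questionnaire on "Parents prior beliefs about the short-term and long-term success and burden of dietary intervention and CAU". Table 3 lists it at T0 and T1 among the descriptives. The paragraph then gives the score a second use: it "will be used to examine successful randomization, by verifying whether the three groups differ in beliefs about the effectiveness of the intervention at baseline".

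The Randomization section explains that the trial began with three randomised arms and that this was changed after 17 inclusions. The reason given is: "Parents usually had a strong preference towards either a dietary intervention or CAU". Since the change, only the two diets are allocated at random. On the third group the section says: "The non-randomized comparator arm includes children who are being treated with CAU". The Procedures section confirms how families enter it: "Families can choose whether they want to participate in the dietary treatment arms or the CAU arm".

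On timing, Procedures describes an intake at which details are explained, appointments are planned and the researcher is "to disclose which diet the child is randomized to via a sealed envelope". T0 falls in the two weeks before treatment starts.

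**The concern.** A check of randomisation is informative only for groups formed by randomisation. Here one of the three groups is formed by family choice, and the variable compared (beliefs about diet and about CAU) is closely related to that choice. The sentence fits the abandoned three-arm design but stands in the current Methods text.

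If it is followed as written, a belief difference that comes from self-selection into CAU could be reported as doubt about the randomisation of ED against healthy diet, when that randomisation was sound. The trial can ill afford such confusion about expectations. Its Background criticises earlier studies for unequal parental expectations, and its own primary outcome uses ratings by parents who know the allocation.

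**Working it through.** The article gives no figure for this check, so there is none to reproduce. The main argument comes from setting the sections side by side.

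**Which groups were randomised**

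| Group | How formed (Randomization, Procedures) | In the check (Prior beliefs) | Can it inform on randomisation? |
|---|---|---|---|
| ED | Random, 50:50 against healthy diet | Yes | Yes |
| Healthy diet | Random, 50:50 against ED | Yes | Yes |
| CAU | Family choice | Yes | No |

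Of the three pairwise contrasts, only ED versus healthy diet bears on the randomisation. The two contrasts with CAU describe self-selection.

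**Illustration of size**

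Inputs from the document: 81 children in each diet group (Sample size and power) and 60 in CAU (Abstract), so N = 222.

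Assumptions: a one-way three-group F test at 5%; equal mean beliefs in ED and healthy diet; CAU shifted by d standard deviations. The article names no test for this check and gives no belief means or SDs, so d is shown over a range.

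With means 0, 0 and d, the noncentrality parameter is

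λ = d² × (162 × 60) / 222 = 43.78 d².

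The degrees of freedom are 2 and 219, and the 5% critical value is F = 3.04. The probability of a significant result is P(F′(2, 219, λ) > 3.04), where F′ is the noncentral F distribution.

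| d (SD, assumed) | λ | Chance that the three-group test reports a difference |
|---|---|---|
| 0 | 0 | 5% |
| 0.2 | 1.75 | 20% |
| 0.3 | 3.94 | 41% |
| 0.5 | 10.95 | 85% |
| 0.8 | 28.02 | 99.8% |

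The two diet groups have identical beliefs in every row. A test of ED versus healthy diet alone, on beliefs recorded before disclosure, would report a difference in 5% of trials in every row, whatever CAU parents believe.

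**Timing (conditional)**

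Procedures has the envelope opened at the intake where appointments are planned. Table 3 puts the belief form at T0. Read in order, disclosure comes first and T0 follows, but no section places the form relative to the envelope.

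If the form does follow disclosure, suppose that knowing the diet shifts ED against healthy-diet beliefs by e SD. For 81 versus 81, λ = e² × 81 × 81 / 162 = 40.5 e², with 1 and 160 degrees of freedom and critical value 3.90.

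| e (SD, assumed) | λ | Chance that the two-group test reports a difference |
|---|---|---|
| 0.2 | 1.62 | 24% |
| 0.3 | 3.65 | 48% |
| 0.5 | 10.13 | 89% |

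In that case, dropping CAU from the check would not be enough to make it a test of allocation.

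**The case against.** The strongest reply is that this is a descriptive item with little resting on it. It is listed under Descriptives, and no estimate, stopping rule or treatment decision in the article uses it. Readers are told plainly that CAU is not randomised. No test or threshold is stated either. A table of pairwise comparisons would show ED against healthy diet directly, and the percentages above would not apply to it. All of this stands, and it limits the severity. It does not make the sentence right, because the sentence ties success of the randomisation to a comparison of all three groups.

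A reader might go further in four ways that the document does not support:

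- **That the check is bound to signal failure.** The size of the belief difference is unknown. At an assumed 0.3 SD the illustrative test finds nothing in 59% of trials.
- **That the groups must differ in beliefs about effectiveness.** The article reports a strong preference, not its cause. Preference could rest on expected burden, which the questionnaire also covers.
- **That beliefs are certainly recorded after disclosure.** The order in Procedures suggests this, but questionnaires are completed online, the sequence within the T0 window is not stated, and the flowchart (Figure 1) is not reproduced in the text available.
- **That the belief measure is wasted.** The randomisation check is an additional use. The scores are collected at T0 and T1 in any case and remain available for comparing expectations between the diets. How far they capture expectancy about the assigned diet is uncertain, since the items are described as covering dietary intervention in general.

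**Conclusion.** The inconsistency is explicit: a check of randomisation includes a group that was never randomised. A difference involving CAU is likely, given the preferences the article reports, and it is uninformative about the allocation of ED and healthy diet. The figures of 41%, 85% and 99.8% show how easily self-selection alone could produce a difference. They depend on an assumed 5% three-group test and assumed shifts of 0.3, 0.5 and 0.8 SD.

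The timing point holds only if the form is completed after the envelope is opened. In that case a difference between the two diets should be read as expectancy after disclosure and not as failed allocation.

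The primary ED versus healthy diet analysis is unaffected. This is a minor correction.

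**What to change.** Replace the three-group comparison with ED versus healthy diet wherever beliefs are used to judge the randomisation. Report CAU beliefs separately, labelled as a description of self-selection. This changes one sentence and costs nothing.

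State when the belief form is completed relative to disclosure of the diet. If it comes afterwards, interpret any ED versus healthy-diet difference as expectancy, and have parents in the remaining enrolment complete the five items before the envelope is opened. The cost is moving a short form. The drawback is that children already enrolled have only the later score, so the two sets should be reported separately and only the pre-disclosure scores used to judge the allocation.
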